**OSCAR – OSNABRÜCK STUDY ON CARDIAC ARREST**

**Study protocol**

Introduction

In particular, the quality of chest compression quality during resuscitation was identified as an influencing factor for survival of cardiac arrest (1,2,3,4). Pre-hospital as well as in-hospital studies with professional medical staff show sobering quality results. Thorax compression depth and frequency did often not meet the guidelines (2.4) and chest compression was frequently discontinued resulting in blood flow arrest (5). Even emergency medical personnel trained on the guidelines were unable to comply with the required recommendations for resuscitation quality in resuscitation scenario (2,4,5). In a study from Norway, no rescue team reached the required guidelines recommendations on resuscitation quality (6). Both from safety-relevant fields of work such as power plants or aviation (7), as well as from acute medical work areas is known that stress can lead to a limitation of perception. Von Rittenberger were able to show this for behavior in cardiac arrest situations. With increasing complexity, the performance of Emergency medical staff deteriorated in simulated resuscitation scenarios (8).

In order to optimize the chest compression quality, the industry has developed in recent years measuring instruments that can measure the chest compression depth and frequency as well as the interruption of compression during resuscitation. If deviations from the standard occur when using these devices, audiovisual feedback is given to the staff. In addition, these devices record data from the entire course of the resuscitation and thus allow an evaluation. These devices have been named real-time feedback system (RTF)(9). The aim of using real-time feedback systems is to comply with the guidelines for chest compression depth and frequency and to minimize interruptions in compression. The current reanimation guidelines published in 2010 emphasize the importance of ensuring "high-quality resuscitation" as one of the most important predictors of patient survival (10,11). The guidelines provide a chest compression depth of 5 - 6 cm for adult resuscitation, followed by total chest relief.

The reason for this demand for thorax compression depth is the correlation between thoracic compression depth and resuscitation success, which has been documented in different studies (4,12). Furthermore a frequency of 100 - 120 chest compressions per minute should be maintained (10,11). Any disruption of chest compression results in a decrease in coronary and cerebral perfusion pressure and decreases the chances of survival (3,13,14), interruptions, for example for ECG interpretation, remain restricted to a minimum and are only advised at the end of a resuscitation cycle (10). The duration of a cycle is set to two minutes.

Aim/Hypothesis:

Compared with conventional resuscitation, a real-time feedback system changes the quality of resuscitation in out-of-hospital cardiac arrest when considering compression depth, rate, and pauses in compression.

Endpoint:

1.Primary Endpoint:

1.1. Change in the quality of resuscitation (compression depth, frequency and pauses in compression).

1.2. Reaching the recommended target parameters set by the guidelines of the European Resuscitation Council (ERC) for compression depth, frequency and pauses in compression.

2.Secondary Endpoint:

2.1. Change in short-term survival of resuscitated patients defined as reaching the hospital with return of own circulation (ROSC).

Methods

Ad 1.a compression depth:

The real-time feedback system (RTF) is integrated into a defibrillator (corpuls, Kaufering, Germany) and includes a sternal electrode with accelerometer (CorPatch CPR, corpuls, Kaufering, Germany). The sternal sensor is placed at the pressure point in the middle of the sternum. A piezo crystal is integrated, which is brought by the chest compression in sagittal motion. The RTF records the speed and time of each individual chest compression. From these two variables, it calculates chest compression depth in real time. Thoracic compression depth is recorded with an accuracy of ± 6.25 mm (15,16).

Ad 1.b. compression frequency:

The compression rate is subsequently measured via ECG artifacts from the monitor ECG. For this purpose, the ECG derivation II, by means of the self-adhesive paddles continuously measured and stored on a memory card (CF card). This ECG can be viewed and analyzed using the corView2 software. Chest compressions on the ECG can be distinguished from other electrical actions of the heart.

**ECG Interval with chest compression artifacts (corView2)**

[figure not shown]

Ad 1.c.pauses in compression:

The interruptions of the compression ("hands-off") are subsequently analyzed via artefacts from the ECG.

- Total Breaks: All determined hands-off periods between the first and the last chest compression. A period without chest compression is defined with a threshold of at least 1.5 sec (hands-off periods are periods during which no chest compressions take place)
- Longest pause:

longest Hands-off pause in seconds

- Number of pauses >10s:

Number of all hands-off breaks greater than 10s

- Intermediate time interval until defibrillation ("Pre-Shock Pause"):

Average time in seconds of all pre-shock. Only calculated for hands-off periods with a delivered shock event. If there are multiple shocks within a hands-off period, the first defibrillation will always apply.

- Post-Shock pause:

Average time in seconds of all post-shock breaks. Only calculated for hands-off periods with a delivered shock event. If there are multiple shocks within a hands-off period, the first defibrillation will always apply.

- Peri-Shock pause:

Average time of all hands-off periods with one or more defibrillations.

- chest compression fraction:

Ratio of hands-on time to hands-off time (🡺 the ratio of times in chest compression is performed in relation to the times when no chest compressions is performed.

Ad 2. Short-time survival:

The resuscitation results (short-term survival) are recorded and evaluated in the German Resuscitation Registry®.

Indicators:

- Endpoint 1.1: Detecting a statistically significant change in the aforementioned qualities (chest compression frequency and interruption of compression) to phase 1 in phases 2 and 3. Detecting a change in thoracic compression depth in phases 2 and 3. Interruptions are defined as pauses greater than 1.5 s, in which at the same time the ECG has no indication of a perfusing heart rhythm (18).
- Endpoint 1.2 percent deviation from the ERC guidelines in terms of compression depth: 5.0-6.0 cm (19), compression frequency: 100 / min (19)
- Endpoint 2: Reaching hospital admission with spontaneous circulation (ROSC) documented in the resuscitation registry.

Inclusion criteria:

- All patients with a non-traumatic cardiac arrest who were 18 years old or older at the resuscitation attempt. Excluded are inmates.
- Resuscitations with chest compression time less than one minute are excluded

Design:

The study is build up in three phases:

In the first phase, 95 patient data are included, in phase 2 and 3 92 (total 279). This number of cases is taken from the biometric report. The city of Osnabrück and the district of Osnabrück have a combined population of 506,000 (as of Dec. 2013) (17). Every year about 300-400 out-of-hospital resuscitation attempts can be expected.

- **Phase 1:** Data is recorded without using the accelerometer (real-time feedback system). The analysis of chest compression frequency and interruptions is done via ECG evaluation. The data of the resuscitation register will be used to analyze the clinical data.
- **Phase 2:** Data is recorded using the feedback sensor without giving a real-time feedback to the Emergency medical staff. The analysis of chest compression frequency and interruptions is done via ECG evaluation. The data of the resuscitation register will be used to analyze the clinical data.
- **Phase 3**: Data is recorded using the feedback sensor and the Emergency medical staff receives a real-time feedback on chest compression quality. The analysis of chest compression frequency and interruptions is done via ECG evaluation. The data of the resuscitation register will be used to analyze the clinical data.

Data flow of the device data:

1. The patient data of each resuscitation are loaded via mobile data transfer to a server and is retrieved from there for evaluation. This corresponds to the usual procedure in the rescue services. The resuscitation missions are subsequently identified in the collective of missions.

2. The data for the resuscitation quality are loaded via mobile data transfer to a server and from there after identification of the inserts (see point 1) for evaluation. The data records are sent anonymously to the corpuls company:
[figure not shown]

The anonymization will be done via filters. The individual data are listed below. Any data that could lead to patient identification, directly or in combination with other data, will be removed. The contents are no longer available in the evaluation database and can no longer be retrofitted.

| Patientendaten | | | | |
| --- | --- | --- | --- | --- |
| **Art der Daten** | identifizierend?  [figure not shown] = ja [figure not shown] = evt. resp. in Kombination [figure not shown] = nein | PHI?  [figure not shown] = ja [figure not shown] = evt. [figure not shown] = nein | Maßnahmen | Ergebnis  [figure not shown] = k.P. [figure not shown] = Achtung [figure not shown] = Anw. BDSG |
| **Patienten-ID** | [figure not shown] | [figure not shown] | Daten werden entfernt. | [figure not shown] |
| **Fallnummer** | [figure not shown] | [figure not shown] | Daten werden entfernt. | [figure not shown] |
| **Vorname** | [figure not shown] | [figure not shown] | Daten werden entfernt. | [figure not shown] |
| **Nachname** | [figure not shown] | [figure not shown] | Daten werden entfernt. | [figure not shown] |
| **Geschlecht** | [figure not shown] | [figure not shown] | Daten werden entfernt. | [figure not shown] |
| **Geburtsdatum** | [figure not shown] | [figure not shown] | Daten werden entfernt. | [figure not shown] |
| **Alter** | [figure not shown] | [figure not shown] | Daten werden entfernt. | [figure not shown] |
| **Gewicht** | [figure not shown] | [figure not shown] | Daten werden entfernt. | [figure not shown] |
| **Größe** | [figure not shown] | [figure not shown] | Daten werden nicht erfasst | [figure not shown] |
| **Adresse** | [figure not shown] | [figure not shown] | Daten werden entfernt. | [figure not shown] |
| **Ort** | [figure not shown] | [figure not shown] | Daten werden entfernt. | [figure not shown] |
| **Versicherten-Nr** | [figure not shown] | [figure not shown] | Daten werden entfernt. | [figure not shown] |
| **KK/Kostenträger** | [figure not shown] | [figure not shown] | Daten werden entfernt. | [figure not shown] |
| **Versicherten Karten-Nr** | [figure not shown] | [figure not shown] | Daten werden entfernt. | [figure not shown] |
| **Transportmittel** | [figure not shown] | [figure not shown] | Daten werden entfernt. | [figure not shown] |
| **Funkkennung** | [figure not shown] | [figure not shown] | Daten werden entfernt. | [figure not shown] |
| **Geräte-ID** | [figure not shown]  in Kombination mit Organisation |  | Daten werden entfernt. | [figure not shown] |
| **Zeitpunkt des Gerätestarts (Einsatzstart)** | [figure not shown] | [figure not shown] | identifizierende Daten entfernen, damit sind auch diese Daten kein PHI mehr | [figure not shown] |
| **Dauer des Einsatzes (Einsatzende)** | [figure not shown] | [figure not shown] | identifizierende Daten entfernen, damit sind auch diese Daten kein PHI mehr | [figure not shown] |
| **Seriennummer der einzelnen Gerätemodule** | [figure not shown] |  | Daten werden entfernt. | [figure not shown] |
| **Seriennummer der einzelnen Geräteoptionen** | [figure not shown] |  | Daten werden entfernt. | [figure not shown] |
| **Kontinuierlich aufgezeichnete Kurven** | [figure not shown] | [figure not shown] | identifizierende Daten entfernen, damit sind auch diese Daten kein PHI mehr | [figure not shown] |
| **Kontinuierlich aufgezeichnete Vitalparameter** | [figure not shown] | [figure not shown] | identifizierende Daten entfernen, damit sind auch diese Daten kein PHI mehr | [figure not shown] |
| **12-Kanal-EKG** | [figure not shown] | [figure not shown] | identifizierende Daten entfernen, damit sind auch diese Daten kein PHI mehr | [figure not shown] |
| **12-Kanal-EKG Vermessung, Diagnose und Therapieempfehlung (HES)** | [figure not shown] | [figure not shown] | identifizierende Daten entfernen, damit sind auch diese Daten kein PHI mehr | [figure not shown] |

Data flow of patient data:

The mission is documented in the German Resuscitation Register and retrieved from there for evaluation. In the resuscitation register, the mission is pseudonymised stored under a mission number and can be retrieved from there for evaluation on the application number, without the data that allows a direct identification of the patient can be accessed.

Matching patient and device data:

The matching takes place on a computer of the University Hospital Münster as shown.

Statistics:

The statistical calculations were based on the knowledge from the study Kramer Johansen et al. "Quality of out-of-hospital cardiopulmonary resuscitation with real-time automated feedback: a prospective interventional study".

1. Endpoint 1.1: Phase 1 data are used as a reference for chest compression frequency and pauses in compression; Phase 2 data is used as a reference for the depth of compression. These phases are compared with the subsequent phases relating to quality.
2. Endpoint 1.2: The data is assessed phase-specifically for the percentage deviation from the ERC Reanimation Guidelines recommendations.
3. It is analysed whether phase-specific differences in short-term survival are recognizable.

Kompressionsfrequenz

Unterbrechung der Kompression

Kompressionstiefe

Phase 2

Phase 1

Phase 3

Phase 2

Phase 3

The multiple significance levels are set at 5%, and the power should always be ≥ 80% (error 2nd type ≤ 20%).

There are one or more comparisons for each target size. The multiple significance level of 5% is divided into Bonferronie targets in three parts (weighted):

1. For the comparisons concerning the depth of the compression, a local significance level of 1/4 * 5% is used. Here only the groups Phase 2 and Phase 3 are compared with each other with respect to the Mann-Whitney-U-test for the local significance level 1/4 * 5%.
2. For the comparisons regarding the compression frequency, a local significance level of 1/4 * 5% is used. Here the groups Phase1, Phase 2 and Phase 3 are compared with each other in pairs to the local significance level 1/4 * 5%. This results in 3 group comparisons. The multiple test problem is solved here by using the final test (for the pair comparisons the Mann-Whitney U test is used, for the 3 group comparisons (cutting hypothesis) the Kruskal-Wallis test is used).
3. For the comparisons concerning pauses in compression, a local significance level of 1/2 * 5% is used. Here, the groups Phase1, Phase 2 and Phase 3 are compared with each other in pairs to the local significance level 1/2 * 5%. This results in 3 group comparisons. The multiple test problem is solved here by using the final test (for the pair comparisons the Mann-Whitney U test is used, for the 3 group comparisons (cutting hypothesis) the Kruskal-Wallis test is used).

Powercalculation and number of cases:

The Phase 1 treatment group requires 95 patients, the Phase 2 treatment group requires 92 patients, and the Phase 3 treatment group requires 92 patients. In total, 95 + 92 + 92 = 279 patients are needed for this project.

1. For the comparisons of compression depth, with these numbers of patients a power of 82.1% is achieved.
2. For the comparisons of compression frequency, a power of 86.5% is achieved with these patient numbers (= probability that all three pair comparisons will yield a significant result).
3. For the comparisons of pauses in compression, with these patient numbers a power of 80.1% is achieved (= probability that all three pair comparisons yield a significant result).

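### Primary Endpoint 1.2 takes a single 100/min as its frequency reference, while the protocol quotes the guideline as 100–120/min, and no deviation formula is given

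*Supplement*

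**What the plan says.** The Endpoint section lists 1.2 as primary and defines it as "Reaching the recommended target parameters set by the guidelines of the European Resuscitation Council (ERC) for compression depth, frequency and pauses in compression". The Indicators section turns this into a measure: "percent deviation from the ERC guidelines in terms of compression depth: 5.0-6.0 cm (19), compression frequency: 100 / min (19". The Statistics section adds only this for Endpoint 1.2: "The data is assessed phase-specifically for the percentage deviation from the ERC Reanimation Guidelines recommendations".

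The Introduction gives the guideline values that the trial relies on. For depth it says: "The guidelines provide a chest compression depth of 5 - 6 cm for adult resuscitation". For frequency it says: "Furthermore a frequency of 100 - 120 chest compressions per minute should be maintained (10,11".

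So the depth reference is the same range in both places. The frequency reference is a range in the Introduction and a single number in the Indicators.

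**The concern.** Endpoint 1.2 is meant to show how closely crews keep to the guideline in each phase. If the reference is a point at the lower edge of the range that the protocol itself quotes, a resuscitation in the middle of that range is recorded as deviating. The Introduction names guideline compliance as the aim of feedback devices. A measure that can count movement into the quoted range as a departure from target would not serve that aim.

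The missing formula adds to this. Without a stated reference, sign convention and unit of analysis, the choice could be made after the phase data have been seen, in a design of three phases defined by how the feedback device is used.

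**Working it through.** The plan states no figure for Endpoint 1.2, so there is none to reproduce. The check scores the same rates under each reading of the text.

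**Inputs**
- Reference in Indicators, Endpoint 1.2: 100/min.
- Guideline in Introduction: 100–120/min.
- Scoring rule: none given. The three rules below are candidate readings.

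**Formulas, for a rate r per minute**
- Point target: 100 × (r − 100) / 100.
- Range: 0 if 100 ≤ r ≤ 120; 100 × (r − 100) / 100 below; 100 × (r − 120) / 120 above.
- Minimum: the point formula below 100; 0 otherwise.

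| Rate (/min) | Point target | Range | Minimum |
| --- | --- | --- | --- |
| 90 | −10% | −10% | −10% |
| 95 | −5% | −5% | −5% |
| 100 | 0% | 0% | 0% |
| 105 | +5% | 0% | 0% |
| 110 | +10% | 0% | 0% |
| 115 | +15% | 0% | 0% |
| 120 | +20% | 0% | 0% |
| 125 | +25% | +4.2% | 0% |
| 130 | +30% | +8.3% | 0% |

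The point target parts from the quoted guideline from 101 to 120/min. The minimum agrees with it there but parts from it above 120/min. Only the range rule agrees with the Introduction throughout.

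**Absolute or signed.** With absolute values under the point target, 110/min and 90/min both score 10%, and 95/min scores 5%. With signed values the direction is visible, but a phase average can cancel: equal numbers of cases at 90 and 110/min average (−10 + 10) / 2 = 0%.

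**Illustration by phase.** The protocol gives no expected rate or SD for any phase. The normal distributions below are therefore assumptions. The entries are mean absolute deviations.

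| Assumed mean, SD | Point target | Range | Share of rates in range |
| --- | --- | --- | --- |
| 100, 5 | 4.0% | 2.0% | 50% |
| 100, 15 | 12.0% | 6.5% | 41% |
| 110, 5 | 10.1% | 0.1% | 95% |
| 110, 10 | 11.7% | 1.5% | 68% |
| 110, 15 | 14.5% | 4.2% | 50% |
| 120, 20 | 23.3% | 8.3% | 34% |

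At SD 15, a phase centred at 110/min is worse than one centred at 100/min on the point measure (14.5% against 12.0%) and better on the range measure (4.2% against 6.5%). At mean 110 and SD 10 it is about level with the 100/min, SD 15 phase on the point measure (11.7% against 12.0%) and clearly better on the range measure (1.5% against 6.5%).

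**Reach.** The Statistics section divides alpha as 1.25% for depth, 1.25% for frequency and 2.5% for pauses, which sum to 5%. The Mann-Whitney U and Kruskal-Wallis tests compare phases with each other, not with a guideline value. The planned Hodges-Lehmann estimates are also differences between groups. None of these uses 100/min. The stated powers (82.1%, 86.5% and 80.1%) and the total of 95 + 92 + 92 = 279 patients belong to those comparisons.

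**The case against.** The strongest reply is that the harm depends on a formula that the protocol does not contain. It does not say whether the deviation is signed or absolute, whether it is taken per case or on the phase average, whether the percentage of deviating cases is meant, or whether 100/min is a minimum. A reader might infer that the plan definitely scores on-target resuscitations as off target. The text does not support that much: under the minimum reading, 101–120/min does not deviate. This part of the reply stands, and it makes the consequence conditional. It does not remove the conflict, because the minimum reading leaves rates above 120/min unscored, against the range in the Introduction.

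A reader might also infer that the ranking of the phases will reverse. The documents cannot show that. The contrast of 95 with 110/min and the distributions in the check are assumptions, and the reversal arises with absolute deviation from a point.

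Finally, the two figures cite different sources: the 2010 European guideline sections in the Introduction, and an undated guideline website entry in the Indicators. Neither can be consulted here, so the review cannot say which figure is right. That stands too. It is a reason to reconcile the sections, not to leave both in place.

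**Conclusion.** The inconsistency is real and nothing elsewhere in the protocol resolves it. The measure for a primary endpoint uses a frequency reference that disagrees with the protocol's own account of the guideline, and its formula is missing. On the literal point reading, rates that meet the quoted guideline score a deviation of up to 20%. On the minimum reading, the upper limit of the quoted range is lost.

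Because Endpoint 1.2 is labelled primary, a reader might conclude that the trial's main inference is compromised. The documents do not support this. Endpoint 1.2 is only assessed by phase, with no test assigned to it, and the Endpoint 1.1 tests, alpha split, stated powers and sample size are unaffected. Rates are recorded in all three phases, so either reference can be applied to data already planned. The point should be fixed, but it does not undermine the design.

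**What to change.** Reconcile the Introduction with the Indicators so that Endpoint 1.2 uses one frequency reference, and state the formula: point, minimum or range; signed or absolute; per case or per phase; and the treatment of values inside a range.

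If the quoted range stands, score frequency as zero inside it and as percent distance to the nearest limit outside it. Write down the same rule for depth, since the protocol lists a depth range but no scoring rule. Reporting the percentage of cases inside each range would be a useful optional addition.

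The cost is about one line of protocol wording. No new data and no change to the sample size are needed.

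### Compression rate and pauses are scored afterwards from ECG artefacts with no provision for masking the scorer to phase, so differential scoring between phases cannot be excluded

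*Supplement*

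**What the plan says.** **Rate.** Protocol, Methods, Ad 1.b: "The compression rate is subsequently measured via ECG artifacts from the monitor ECG". On the tool: "This ECG can be viewed and analyzed using the corView2 software". The section adds: "Chest compressions on the ECG can be distinguished from other electrical actions of the heart".

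**Pauses.** Under Ad 1.c, interruptions "are subsequently analyzed via artefacts from the ECG", with a threshold of at least 1.5 s. Under Indicators, a pause must exceed 1.5 s and must be one "in which at the same time the ECG has no indication of a perfusing heart rhythm".

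**Phases.** According to Design, Phase 1 runs without the accelerometer, Phase 2 with the sensor but no feedback, and Phase 3 with both. For all three, rate and interruptions are to come from the ECG. The Statistics section compares the reference phases with those that follow.

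**Data handling.** Under Data flow of the device data: "The data records are sent anonymously to the corpuls company". The filter is meant to prevent identification of the patient. Its table marks patient, device and vehicle identifiers for removal. For device start time, mission duration and the continuous recordings ("Kontinuierlich aufgezeichnete Kurven"), it says only that identifying content is taken out so that the rest no longer counts as protected health information. Patient and device data are matched on a computer of the university hospital.

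**Scoring.** The protocol does not say who or what scores the ECG, or whether the scoring is masked to phase.

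**The concern.** Depth is calculated by the device in real time. Rate and pauses are reconstructed later, and that leaves room for judgement: which deflections are compressions and which are cardiac activity, where a gap begins and ends, and whether the rhythm looks perfusing.

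The phases are not randomised. A contrast between them is credible only if the measurement works identically in each. A scorer who knows the phase may resolve doubtful stretches differently. A scorer who can see a sensor channel in Phases 2 and 3 has direct timing of compressions that is absent in Phase 1. The first route could affect any comparison. The second would set Phase 1 apart from both later phases and would arise even with a disinterested scorer.

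A systematic scoring difference is not reduced by more patients or a stricter significance level. It has to be prevented at the scoring step.

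**Working it through.** The protocol states no figure for scoring error, so there is none to reproduce. The check has four parts.

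**1. How much of the confirmatory analysis depends on ECG scoring** (Statistics)

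| Measure | Share of 5% | Local level | Pairwise comparisons | Source |
|---|---|---|---|---|
| Depth | 1/4 | 1.25% | 1 | device, real time |
| Rate | 1/4 | 1.25% | 3 | ECG, afterwards |
| Pauses | 1/2 | 2.5% | 3 | ECG, afterwards |

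The levels add up: 1.25% + 1.25% + 2.5% = 5%. ECG-scored measures hold 1/4 + 1/2 = 3/4 of the level (3.75%) and 3 + 3 = 6 of the 7 pairwise comparisons.

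**2. Whether phase could be inferred from a record**

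- Calendar date: the phases are sequential, so a date points to a phase. Start time is not listed as removed. The measure entered for it can mean that date elements are stripped, or that the field stays once other identifiers are gone.
- Sensor channel: present only in Phases 2 and 3. The table does not name it. It may fall under the continuous recordings, which are also not listed as removed.
- Phase label: not mentioned in the filter.

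Inference of phase is therefore probable but not stated.

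**3. What a scoring shift would do to the tests (assumed shifts)**

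Inputs: group sizes 95, 92 and 92; the planned closed test (Kruskal-Wallis, then Mann-Whitney U, each at the local level); normal data; no true effect; Phase 3 scores shifted by a fixed fraction of the SD; 3,000 simulated trials per setting. The result is the proportion with at least one significant comparison involving Phase 3.

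| Assumed shift | Rate (level 1.25%) | Pauses (level 2.5%) |
|---|---|---|
| 0 | 1.1% | 2.4% |
| 0.1 SD | 2.5% | 4.9% |
| 0.2 SD | 10.6% | 16.5% |
| 0.3 SD | 33.0% | 40.4% |

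The largest simulation standard error is √(0.404 × 0.596 / 3000) ≈ 0.009, or 0.9 percentage points.

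**4. What a spurious minimum-length gap would do to hands-off time**

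One false 1.5 s gap per minute adds 1.5/60 = 2.5 percentage points; two add 3.0/60 = 5.0; three add 4.5/60 = 7.5. At the guideline rate of 100–120 per minute, compressions are 60/120 = 0.5 s to 60/100 = 0.6 s apart. One missed compression leaves 1.0–1.2 s, below the threshold. Two consecutive misses leave 1.5–1.8 s. Each false gap thus needs at least two consecutive misses. At exactly 1.5 s it counts under Ad 1.c but not under Indicators, so the two pause rules can score the same trace differently.

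**The case against.** The strongest reply is that the protocol prescribes the same ECG method for all three phases and never says that the sensor channel is viewed during scoring. Scoring may be automatic, which would leave little room for knowledge of phase. No separate analysis plan is shown, so silence about the scorer is not in itself a fault. This stands, and it limits the point to a missing protection. It does not remove the point: a common method is not a masked one, and the pause definition includes a reading of the rhythm.

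A reader might go further and infer any of the following. The documents do not support them.

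- *That the scorer sees the phase.* This is nowhere written. The start-time measure is ambiguous, and the table names no sensor channel.
- *That the manufacturer scores the endpoints.* The readable text gives no purpose for the transfer. The sentence leads into a figure that is not shown, and matching takes place at the university hospital.
- *That scoring favours the feedback phase.* No direction is shown. Extra sensor information would separate Phase 1 from Phases 2 and 3 alike and would give Phase 3 no advantage over Phase 2, the contrast that isolates feedback.
- *That hands-off time is off by 2.5 to 7.5 points.* That needs at least two consecutive misses, one to three times every minute, in Phase 1 only. Nothing in the documents suggests such a frequency. Isolated 1.5 s gaps would also not create pauses over 10 s and would rarely set the longest pause.
- *That the problem could never be checked later.* The ECG is stored and could be re-read masked.

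**Conclusion.** The point holds as a design weakness with an inexpensive remedy. Two of the three primary quality measures, with 3.75 of the 5 percentage points of significance level and six of seven pairwise comparisons, rest on retrospective ECG scoring for which no masking to phase is provided. Phase could probably be inferred from date or sensor channel, so differential scoring cannot be excluded.

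Whether it occurs, how large it is and which way it goes are all unknown. The simulated rates (10.6% for rate and 16.5% for pauses at 0.2 SD) rest on an assumed shift in Phase 3 and normal data. They show only that a modest systematic difference would matter if it arose. Depth is not affected. The manufacturer's role is undefined in the readable text, which calls for a clarifying sentence and does not show bias.

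**What to change.** Extend the existing filter and fix the scoring procedure in the protocol:

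1. Score rate and pauses from files that hold only a study number, the ECG, shock-event markers and time relative to device start. Remove calendar date, phase and sensor channel. The shock markers must stay, because the pre-, post- and peri-shock pauses depend on them.
2. Keep the key at the university hospital, where matching already takes place.
3. Score in random order across the three phases, with one common reader or algorithm, and state which.
4. Choose one pause rule, reconciling Ad 1.c and Indicators on the 1.5 s boundary and the rhythm condition.
5. After scoring, compare the masked ECG rate and pauses with the accelerometer in Phases 2 and 3 and report the agreement. This checks Phase 1 only indirectly, since it has no sensor.
6. State in a sentence what the manufacturer does with the records and whether it takes any part in scoring.

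The cost is a filter setting and a random reading order. No extra reader and no new data are needed. The downside is that final scoring waits until the Phase 3 recordings are complete.
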